### Notes Regarding the non-NINDS/non-PROMIS measures

Reduced work productivity is a major consequence of poorly treated migraine and an outcome that may be amenable to a mind–body intervention such as MBSR. To measure this construct, we use the well-validated Work Productivity and Activity Impairment instrument (WPAI), which is widely used in the work productivity literature [23] and has been advocated specifically for use in migraine studies [24]. The Perceived Stress Scale (PSS-10) is the most widely used instrument for assessing perceptions of stress and has been used successfully in prior studies of meditation [25, 26]. The Mindful Attention Awareness Scale (MAAS) was developed as a global measure of mindfulness and has been successfully validated for use in clinical studies [27, 28].

#### Medication use

Data are collected on the use of analgesics and migraine-specific preventive and rescue medications using the 31-day headache diaries at all visits. There are no study medication restrictions; the protocol does not attempt to influence medications prescribed by the participants’ physicians. Medication use by all participants is tracked with questionnaires and by extracting all dispensed prescription medications from the EHR of both health systems.

#### Actigraph

Each participant is asked to wear an actigraph (GENEActiv™ accelerometer; Activinsights, Kimbolton, Cambridgeshire, U.K.) on their wrist for 2 weeks at baseline and for 2 weeks at the 3-month visit. The actigraphy data (an exploratory outcome) is collected for objective assessments of sleep quality in both groups.

#### Closeout interviews

We will conduct a single focus group with a random sample of participants who completed all phases of the study to gain a better understanding of the qualitative aspects of the trial and to learn about participants’ experience with their MBSR classes and which aspects of the trial were particularly successful and which could be improved. In addition, we will individually interview up to 10 participants who did not complete the study to gain a better understanding of personal barriers to successful completion.

### Clinic procedures and assessment schedule

This trial includes a telephone screening call, an eligibility screening visit, a 1-month (31-day) run-in period, a randomization visit, then an 8-month follow-up period that includes four in-person visits. The content of each assessment is described below, and the timing described in the Spirit figure (Additional file 1; Fig. 2). The workflow of randomized participants is illustrated in Fig. 1.

**Fig. 2 Fig2:**
[figure not shown]
SPIRIT figure. HIPAA Health Insurance Portability and Accountability Act, MBSR Mindfulness-based stress reduction

#### Telephone screen

All potentially eligible patients who are interested in the study are screened by telephone interview. The telephone screen informs potential participants about the trial, answers any potential questions, and determines whether participants meet telephone-assessable inclusion and exclusion criteria. Study staff track and record information in a recruitment log on every telephone screen conducted. If the potential participant meets the preliminary eligibility criteria based on the telephone screen, they may continue the study eligibility process with an in-person first screening visit.

#### Initial assessment

The initial assessment takes place over a 31-day run-in period. This multi-component procedure evaluates a potential participant’s study commitment and confirms their eligibility. This process includes a first screening visit and an enrollment and randomization visit.

#### First screening visit

The first screening visit is scheduled during the telephone screen and takes approximately 1 hour. At this visit, all eligibility criteria are reviewed and validated, and the potential participant’s commitment and availability are assessed. Potential participants who meet the initial study criteria are given a copy of the informed consent form, and the study staff reviews the document with them. If they agree to and sign the consent form, they are invited to begin the run-in period. This screening visit is conducted by a study coordinator who is trained in both clinical trials and in MBSR.

#### Run-in period

Consented participants begin the 31-day run-in period prior to randomization. Patients in this phase complete a daily headache diary containing five questions related to headache frequency and severity, and medication use. Participants are also given an actigraph to wear for the first 14 days of the run-in period.

#### Enrollment and randomization visit

Participants who record between 4 and 14 headache days during the run-in period are eligible to proceed to randomization. Study participants are randomized into one of two study arms: (1) the MBSR intervention plus usual care or (2) usual care alone. Participants complete questionnaires regarding their health and headaches, which take less than 30 min to complete.

#### Intervention period

Participants randomized to the MBSR arm are registered to attend a public MBSR class. In most cases, there is a waiting period of up to 3 months before the class begins. The 8-month follow-up period begins on the official first MBSR class date. Participants have the option to conduct the intervention-period study visits virtually.

#### Follow-up visits

Three months after the start of the MBSR classes, participants attend for a follow-up visit and are asked to wear the actigraph again for 14 days. We collect any feedback on the MBSR class for those in the intervention arm. The second headache diary (for measurement of the primary study outcome) is provided.

Four months after the start of the MBSR classes, participants attend for a follow-up visit. They return their actigraph and the second headache diary, and complete the online questionnaires. They are also asked about any adverse events.

Six months after the start of the MBSR classes, participants attend for a follow-up visit. They return their third headache diary and complete the online questionnaires. They are asked about any adverse events.

Eight months after the start of the MBSR classes, participants attend for a follow-up visit. They return their fourth and final headache diary and complete the online questionnaires. They are asked about any adverse events. Participants in the control group are offered the MBSR course, and all participants are asked if they would be willing to take part in a focus group.

#### Retention and adherence to MBSR

For each follow-up visit, telephone calls are made to arrange a visit time. The study research assistant will make phone calls until the participant is reached and an appointment is scheduled. After the follow-up window is closed, if the participant has not been contacted, or they have asked to be dropped from the study, the participant is marked as a withdrawal.

The teachers of the individual MBSR classes are asked to handle absenteeism as usual, and provide attendance records for their students in this study.

#### Compensation

Participants are compensated $25 for completing the 4-month data collection, $50 for the 6-month data collection and $100 for the 8-month closeout data collection. Among those individuals who complete all aspects of the study, we will randomly select 15 participants to take part in a focus group for which an additional $100 will be given.

### Statistical procedures

#### Sample size

The sample size of approximately 60 participants for this pilot study was determined in collaboration with the funding agency and was felt to be large enough to gauge whether the community-based classes would be feasible for a full-scale clinical trial intervention. This sample will allow us to estimate an adherence rate of 0.8 with confidence limits ±0.1 around the point estimate.

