### Randomization

Prior to the start of the study, a balanced, blocked randomization list was generated using Stata v14.0 using variable block sizes of 2, 4, and 6 [18]. From the list, a research assistant not affiliated with the study translated the allocation numbers into groups and placed each allocation into an opaque envelope, labeled with a sequential study identifier. The envelopes were then sealed and transferred to the study site.

When each potential participant returns to the clinic with their completed run-in diary (see below), the study staff member verifies their eligibility. If all study eligibility criteria are satisfied, the study staff member opens the next envelope in the sequence and reveals the group assignment to the participant.

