### Study intervention

Participants in the active-treatment group attend a group MBSR class that follows the established protocol for the MBSR intervention as developed by Kabat-Zinn and colleagues at the Center for Mindfulness, University of Massachusetts Medical School [19]. These classes comprise weekly 2.5-h group sessions and a 1-day weekend retreat conducted by a trained MBSR teacher. As this study is designed as a pragmatic trial, participants attend a community-based class for which the instructor and the curricula have been vetted by the study MBSR expert (RS). There are numerous class options for participants within and outside the participating health systems and participants are free to choose any of the approved classes that best matches their availability. The cost of the MBSR classes is covered by study funds. A participant is considered to have successfully adhered to the intervention if they attend at least five of the eight weekly sessions and the 1-day weekend retreat (attendance records are provided by the MBSR instructors). The active treatment is in addition to usual care. The fidelity of the instructor to the vetted curricula was not monitored because of the large number of class options and the potential for such monitoring to become burdensome or intrusive.

Participants randomized to the control arm will continue with their usual activities and complete the study data-collection activities on a schedule identical to that of the MBSR-allocated participants. After the 8-month study period has passed, control-group participants are offered the opportunity to enroll in one of the approved community-based MBSR classes with costs covered by study funds (i.e., a wait-list control).

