### Outcome measures

There are two sets of outcome measures for this pilot trial: those relevant to the feasibility objectives (recruitment and intervention adherence) and those relevant to the effectiveness of the MBSR intervention. Explicit criteria for judging the success of the proposed trial methods have been established a priori. Study methods will be deemed successful within each of the following attributes:Recruitment: Enrollment of at least 60 participants within any 36-week period or enrollment of at least 18 participants within any 9-week period.Intervention adherence: At least 80% of intervention-allocated participants completed at least five of the eight weekly MBSR classes and the 1-day weekend retreat.Primary effectiveness outcome: The primary outcome for assessing the clinical effectiveness of the MBSR intervention is the change in frequency of migraine episodes from baseline as measured by a 31-day headache diary at 4 months.Secondary effectiveness outcomes: Secondary measures of intervention effectiveness were selected to capture specific clinical and quality-of-life attributes that may be affected by the MBSR intervention. All secondary outcomes described below are collected and managed using Research Electronic Data Capture (REDCap) tools hosted at Sutter Health [20]. REDCap is a secure, web-based application designed to support data capture for research studies, providing (1) an intuitive interface for validated data entry, (2) audit trails for tracking data manipulation and export procedures, (3) automated export procedures for seamless data downloads to common statistical packages, and (4) procedures for importing data from external sources.Questionnaire Assessments: Questionnaires were chosen to harmonize with the National Institutes of Health (NIH) Patient-reported Outcomes Measurement Information System (PROMIS) measures [21] and the National Institute of Neurological Disorders and Stroke (NINDS) Common Data Elements for Headache Studies [22], supplemented with additional instruments to assess specific domains and for compatibility with prior migraine trials. All instruments are self-administered, and the total respondent burden was kept to less than 30 min. All instruments have undergone psychometric testing and have been found to be acceptable in terms of internal consistency, content validity, concurrent validity, and test–retest reliability. The instruments are summarized in Table 1.

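### The ±0.1 precision quoted for MBSR adherence matches all 60 participants, but only about 30 can contribute to that rate, so the half-width is about ±0.14

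*Protocol article*

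**What the plan says.** The Sample size section sets the total: "The sample size of approximately 60 participants for this pilot study". It explains that this number was agreed with the funding agency and judged sufficient to show whether community classes are workable for a full trial. It then adds one quantitative statement: "This sample will allow us to estimate an adherence rate of 0.8 with confidence limits ±0.1 around the point estimate". No confidence level or interval method is given.

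The adherence criterion under Outcome measures is: "At least 80% of intervention-allocated participants completed at least five of the eight weekly MBSR classes and the 1-day weekend retreat". The Study intervention section defines adherence for the individual participant in the same terms, by attendance at the weekly sessions and the retreat.

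On allocation, the Randomization section states: "a balanced, blocked randomization list was generated using Stata v14.0 using variable block sizes of 2, 4, and 6". The section on the enrollment and randomization visit confirms two arms: "Study participants are randomized into one of two study arms: (1) the MBSR intervention plus usual care or (2) usual care alone". Controls have no MBSR class to adhere to during the study: "After the 8-month study period has passed, control-group participants are offered the opportunity to enroll in one of the approved community-based MBSR classes".

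**The concern.** The precision statement refers to the whole sample, whereas the quantity being estimated exists in one arm only. If the ±0.1 was worked out on 60, the trial has half the information on adherence that the statement implies.

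This matters because feasibility is the purpose of this pilot. Success thresholds in numbers are set for two attributes only, recruitment and intervention adherence. The precision sentence is also the only statistical support offered for the sample size. A reader who trusts ±0.1 would take an observed 80% to rule out true adherence below about 70%. That reading could carry into the planning of the full trial, including its allowance for non-adherence.

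**Working it through.** **Inputs**

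- Total sample: about 60 (Sample size).
- Adherence rate: p = 0.8, so p(1 − p) = 0.16 (Sample size).
- Denominator: MBSR-allocated participants (Outcome measures).
- Allocation: balanced, two arms (Randomization), so 60/2 = about 30 per arm.
- Confidence level: not stated. I assume two-sided 95% and show 90% and 80% as a range.

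**Formula.** Half-width of the normal-approximation (Wald) interval for one proportion: h = z × √(p(1 − p)/n).

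**Step 1: reproduce the stated figure.** With n = 60 at 95%: h = 1.96 × √(0.16/60) = 0.101. In reverse, h = 0.10 needs n = 1.96² × 0.16/0.10² = 61.5. The stated ±0.1 is therefore what a sample of 60 gives.

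**Step 2: use the protocol's own denominator.** With n = 30 at 95%: h = 1.96 × √(0.16/30) = 0.143. The ratio is 0.143/0.101 = √2, about 41% wider. If the arm ends up between 28 and 32, h runs from 0.148 to 0.139.

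**Step 3: vary the unstated confidence level (Wald, p = 0.8).**

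| Level | n = 60 | n = 30 |
|---|---|---|
| 95% | 0.101 | 0.143 |
| 90% | 0.085 | 0.120 |
| 80% | 0.066 | 0.094 |

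For h = 0.10 with n = 30, z = 0.10/√(0.16/30) = 1.37, a two-sided level of about 83%.

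**Step 4: compare 95% intervals like with like at an observed 80%.**

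| Method | 48/60 | 24/30 |
|---|---|---|
| Wald | 0.699 to 0.901 | 0.657 to 0.943 |
| Wilson | 0.682 to 0.882 | 0.627 to 0.905 |
| Exact (Clopper-Pearson) | 0.677 to 0.892 | 0.614 to 0.923 |

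The lower limit falls by about 0.04 to 0.06, depending on the method.

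**Step 5: size needed for the stated precision.** ±0.10 at 95% needs about 62 participants in the MBSR arm, or about 124 in total at 1:1.

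**Step 6: what the 80% threshold can tell with 30 participants.** The criterion is met when at least 0.8 × 30 = 24 adhere. The binomial probability P(X ≥ 24 | n = 30, p) is:

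| True adherence | Probability of meeting the criterion |
|---|---|
| 70% | 0.16 |
| 75% | 0.35 |
| 80% | 0.61 |
| 85% | 0.85 |

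**The case against.** Several points can be made for the plan.

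- **The confidence level is not given.** This is true, so the comparison depends on assuming 95%. But 30 participants yield ±0.1 only at about 83%, a level hardly anyone uses, and at 90% the half-width is still 0.120. With 60 participants, the conventional 95% gives the figure almost exactly.
- **Rounding.** To one decimal, 0.143 also prints as 0.1. This cannot be strictly excluded, and the text does not say which n was used. It is a strained reading when n = 60 gives 0.101. Even if it were right, readers would take the printed figure as 0.10 and be misled.
- **A different kind of adherence.** The Discussion also speaks of adherence to completing the headache diaries, which would involve all participants. However, 0.8 is the threshold for class attendance, and the sentence just before the precision claim is about the classes.
- **The figure did not determine the sample size.** This stands. The total was settled with the funding agency, so the error lies in the stated precision and not in how the total was chosen.
- **The success rule is a point-estimate threshold.** This also stands: whether it is met does not depend on the interval. What changes is how much meeting it can be taken to show.
- **Pass probabilities go beyond correcting the sentence.** This is fair. They are useful background but are not needed for the correction.

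**Conclusion.** The point holds. For adherence as the protocol defines it, about 30 participants contribute and the precision at a rate of 0.8 is about ±0.14, not ±0.1. This rests on 1:1 allocation of about 60 participants, which the document supports, and on a 95% level, which is assumed. At 90% the stated precision is still missed.

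The error makes the design look better than it is on a central feasibility criterion, so the sentence needs correcting. It does not affect allocation, outcomes, the conduct of the trial or the success threshold itself.

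**What to change.** Replace the precision sentence in the Sample size section with something like this:

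> *Adherence is estimated in the approximately 30 participants allocated to MBSR. An observed rate of 0.8 would have a 95% confidence interval of about ±0.14 (Wilson interval 0.63 to 0.90).*

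Report the adherence result with its 95% interval, Wilson or exact, and name the method. As an option, give the probabilities of meeting the 80% threshold beside the success criterion, so that readers can see how weakly 30 participants separate 75% from 80%.

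The cost is one sentence in the protocol and one interval in the report. The Trial status section says recruitment was completed on 21 September 2018, and no change to enrolment is asked for. The stated precision becomes less favourable.

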#### Statistical analysis

As a pilot trial, the feasibility objectives are central and are focused on recruitment, retention, intervention adherence, and data collection. Recruitment rates are calculated as the mean number of participants enrolled into the trial per week divided by the mean number of patients screened per week. In addition, we examine success in meeting the stated recruitment goals described above. Adherence to the intervention is measured dichotomously (as the proportion satisfying the noted adherence definition) and as the distribution of the proportion of all classes completed. Data-collection success rates are estimated by calculating the proportion of all forms fully completed by participants who remain in the trial (i.e., who have not withdrawn), and the proportion of all forms that should have been completed if retention and data collection were 100%. No formal tests of intervention effectiveness are planned, given the intentionally underpowered pilot nature of the study [29, 30].

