We present here the protocol for a two-arm randomized controlled pilot trial of MBSR for patients with moderate-to-severe episodic migraine headaches. The trial is currently in progress. Should this research prove that it is possible to recruit to a trial of community-based MBSR classes and that the treatment is acceptable to participants, the experience gained from this trial will be used to design and implement a fully powered phase III trial with the objective of testing a low-risk intervention to assist patients who suffer from this often debilitating disorder. As this study contains all the elements of a fully powered trial, but with a single site and smaller sample size, it can be classified as a pilot study [15].

This randomized controlled pilot trial (the Mindfulness and Migraine or M&M study) is designed to assess the achievability and acceptability of an 8-week community-based MBSR intervention for patients with moderate-to-severe episodic migraine. The feasibility outcomes include ability and time required to recruit, adherence to the MBSR treatment, and ability to measure outcomes using 31-day headache diaries and patient-reported questionnaire data. Although we are not measuring efficacy, we will collect clinical outcome data to show the feasibility of our data collection methods. The primary clinical outcome is the change from baseline in headache frequency at 4 months derived from headache diaries. Secondary outcomes include change in headache frequency at 8 months post-randomization and other headache-related measures including headache pain, disability, quality of life, and mental health.

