#### Recruitment at the Sutter Health site

The Sutter institutional review board (IRB) requires active permission from providers for the recruitment of patients into this study. Potentially eligible patients are identified using an EHR-based electronic migraine probability algorithm previously developed and validated by our group [17]. The criteria for active recruitment include a score > 10 from the migraine probability algorithm and an encounter with the site for migraine in the previous 12 months. Providers are given invitation letters for each patient identified and asked to sign those whom they approve. Study personnel then retrieve and mail the signed letters. Each invitation letter contains a return postcard and gives a toll-free number. If patients return the postcard asking to be contacted or they leave a message on the study phone line, the study coordinator calls them for a preliminary screening.

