#### Recruitment at the Kaiser Permanente site

Patients with a history of migraine headache are identified from the EHR. The charts of a random sample of these patients are reviewed by the site’s principal investigator to identify those who have clear evidence of migraine and no EHR-identifiable exclusion criteria. The primary-care physicians for these patients are then contacted and, if there are no objections, each patient is mailed a recruitment letter with an opt-out postcard. Those patients who contact the Kaiser study center are called immediately. Those who do not contact the Kaiser study center and have not returned an opt-out postcard are contacted by phone 3 weeks after the letter is mailed. If a patient passes the telephone screen and expresses interest in participating, their contact information is given to the Sutter Health project coordinator, who contacts the patient and arranges an in-person assessment.

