This protocol describes a pilot trial to compare the effect of community-based MBSR classes with usual care to usual care alone as a preventive treatment for patients with moderately severe migraine headaches. The trial is designed to be highly pragmatic, recruiting a community-based sample of participants with few restrictions on adjunctive therapies and using community-based MBSR classes that represent the typical experience of patients who might choose to practice MBSR for migraine prevention. Thus, the patient population and the intervention are likely to be representative of the usual clinical environment in which such an intervention would be offered. Generalizability is also enhanced by the inclusion of multiple independent recruitment strategies, allowing for comparison of alternative recruitment approaches. The study includes a wide range of clinically relevant outcomes and includes a test of the feasibility of digital-sensor technology (actigraphs) to give a better understanding of the physiological responses to an MBSR intervention.

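### The stated recruitment rate is a screening yield: the weeks cancel, so it cannot show recruitment pace, and the separate week-based goals do not estimate pace either

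*Protocol article*

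**What the plan says.** In the protocol article, the Statistical analysis section defines the recruitment rate as a quotient: "calculated as the mean number of participants enrolled into the trial per week divided by the mean number of patients screened per week". The next sentence adds a second look: "In addition, we examine success in meeting the stated recruitment goals described above". Those goals are set under Outcome measures: "Enrollment of at least 60 participants within any 36-week period or enrollment of at least 18 participants within any 9-week period".

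Time is part of what the pilot is meant to learn. The Background states: "The feasibility outcomes include ability and time required to recruit".

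There are three sources, with different routes to the study:
- **Sutter:** opt-in after provider sign-off. The coordinator calls for a preliminary screening under this condition: "If patients return the postcard asking to be contacted or they leave a message on the study phone line".
- **Kaiser:** opt-out after chart review. "Those who do not contact the Kaiser study center and have not returned an opt-out postcard are contacted by phone", three weeks after the mailing.
- **Community:** flyers and the registry posting.

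The Telephone screen section describes one telephone interview for interested, potentially eligible patients from any source, with each screen entered in a recruitment log. The Recruitment section says the strategies were varied partly to learn which work best for a larger trial. The Discussion counts as a strength the "inclusion of multiple independent recruitment strategies, allowing for comparison of alternative recruitment approaches".

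**The concern.** A rate built from two per-week averages looks like a measure of speed, but dividing one by the other removes the time unit. The only recruitment estimator that the article defines therefore cannot answer one of the pilot's named questions, how long recruitment takes. A full trial needs an expected number randomised per week, with its uncertainty, to set its duration and number of sites. It also needs that figure by source, because the article says the pilot should inform the choice among recruitment strategies. A reader who takes the reported rate as pace could plan on a number that would have been the same had recruitment been twice as fast or twice as slow.

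The formula also leaves open what counts as screened. The article uses the word both for the telephone screen and for the in-person first screening visit, and the denominator could be either.

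**Working it through.** The article gives no numerical recruitment rate, so there is no figure to reproduce. The check is algebra plus the article's own dates and goals.

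**1. The formula.** Let E be the number enrolled, S the number screened and W the weeks observed.

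(E/W) / (S/W) = E/S

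W drops out.

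**2. Illustration.** E = 60 is the planned size (Sample size section). S is not given, so a range is assumed.

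| Assumed S | Ratio at any duration |
|---|---|
| 120 | 60/120 = 0.50 |
| 300 | 60/300 = 0.20 |
| 600 | 60/600 = 0.10 |

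| Duration | Enrolled per week |
|---|---|
| 18 weeks | 60/18 = 3.33 |
| 36 weeks | 60/36 = 1.67 |
| 80.1 weeks | 60/80.1 = 0.75 |

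Each ratio is compatible with every duration.

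**3. Unequal windows.** If screening and enrolment are averaged over different periods, the result is (E/S) × (W_screen/W_enrol). The Trial status section gives first consent on 2 February 2017, first randomisation on 9 March 2017 and end of recruitment on 21 September 2018. That is 85.1 weeks from first consent and 80.1 weeks from first randomisation. Taking first consent as a stand-in for the start of screening, whose date is not given, the factor is 85.1/80.1 = 1.06. This is an effect of the choice of window and does not measure pace.

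**4. What pace would show.** The goals imply 60/36 = 1.67 per week and 18/9 = 2.00 per week. If about 60 were enrolled (an assumption; the final number is not stated), the pace over the reported dates is 60/80.1 = 0.75 per week from first randomisation, or 60/85.1 = 0.70 from first consent. Both are under half of 1.67. The stated ratio could not reveal this.

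**5. What the goals show.** The criterion is met by one good window. Suppose 18 participants were enrolled in one 9-week stretch and the other 42 over the remaining 80.1 − 9 = 71.1 weeks, at 42/71.1 = 0.59 per week. The 9-week goal is passed, yet the overall pace is still 0.75 per week. A pass is therefore compatible with a low average pace.

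**6. Why source matters to the yield.** Assume source yields of 0.30, 0.10 and 0.20, with 300 screened in all. With 200, 50 and 50 screened, the combined value is (60 + 5 + 10)/300 = 0.25. With 50, 200 and 50, it is (15 + 20 + 10)/300 = 0.15. An all-source figure would move with the mix alone. The yields are invented to show the mechanism and are not estimates for this trial.

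**The case against.** The strongest reply is that time is covered. The sentence straight after the formula examines the recruitment goals, which are expressed in weeks, and those goals are the pre-set success criteria. The ratio does not enter them. This stands: it would be wrong to infer that the plan ignores time or that the recruitment verdict is compromised. What the reply does not supply is an estimate, since a best-window pass/fail result gives no average pace and no interval.

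Three further readings are tempting, and the article does not support them.
- **That the rate pools the three sources.** The text speaks of rates in the plural and is silent on pooling. The stated wish to compare strategies points, if anything, towards reporting by source. How a descriptive table is broken down may also be left to a fuller document.
- **That everyone phoned at Kaiser counts as screened, so that its yield is pushed down.** The Telephone screen section ties the screen to interested patients and logs screens conducted. People phoned but not reached, or not interested, need not be in the denominator. The Kaiser section leaves the order of screening and interest slightly unclear, but it does not establish the stronger claim.
- **That letters mailed would be a common starting point.** Sutter letters follow an algorithm score, a recent migraine encounter and active provider approval. Kaiser letters follow random sampling, chart review and absence of physician objection. The pre-selection differs.

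It is also fair to say that different routes into screening are a deliberate design feature, not an analysis error.

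**Conclusion.** The point holds in a limited form. The quantity that the article calls a recruitment rate is a screened-to-enrolled yield. It is invariant to recruitment duration over a common period, and so it cannot describe a named feasibility outcome. The algebra needs no assumption beyond a shared window; with the windows in the article's own dates the departure is a factor of about 1.06. The 0.75 and 0.70 per week figures rest on the assumption that about 60 were enrolled, and the screened counts are illustrative.

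The consequence is modest: a mislabelled and loosely defined descriptive measure, and no stated estimator of average pace. No success criterion, sample size or effectiveness result depends on it. Nor does the article establish a bias between sources. It establishes only that the opt-in, opt-out and self-referral routes select people differently before the shared telephone screen, so yields should not be compared across sources as if like with like.

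**What to change.** Replace the definition in the Statistical analysis section with two measures.
1. **Recruitment pace:** participants randomised divided by weeks of open recruitment, with a 95% confidence interval (an exact Poisson interval would serve), overall and separately for Sutter, Kaiser and community. State the opening and closing dates used for each source.
2. **Screening yield:** enrolled divided by screened, under that name, with the logged telephone screen as denominator, overall and by source. Add a note that the three routes select differently into that screen, so the yields are not directly comparable across sources.

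Leave the 36-week and 9-week goals as they are. Where mailing counts were kept, which the article does not say, letters mailed per participant randomised can be added descriptively for the two health systems, noting the different pre-selection at each.

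The cost is analysis wording and a little more descriptive work. The article already describes a log of every telephone screen and a log of those who decline or are ineligible. Randomisation dates should be in the trial records. The opening date of each source is not printed in the article and would have to be taken from those records.

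Suggested wording: *Recruitment pace is the number randomised per week of open recruitment, with a 95% confidence interval, overall and by source. Screening yield is the number randomised divided by the number of logged telephone screens, overall and by source.*
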